Therefore, the objective of this protocol is to monitor the daily load progression from the basic and intermediate levels to the advanced level by measuring HR, SPE, and HRV for 12 weeks, as well as to analyze the effect of the method on psychometric, cardiorespiratory, and autonomic measures. It is hypothesized that the protocol proposed by the study can be prescribed clinically, proving that SPE, HR, and HRV are useful tools for monitoring the progression of Pilates training loads. Furthermore, SPE is expected to have a good correlation with HR and clinical relevance, thus giving practitioners two simple low-cost monitoring tools. In addition, it is hypothesized that the psychometric, cardiorespiratory, and cardiac autonomic modulation measures will have improved after 12 weeks of training.

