### Participants

A total of 54 healthy male volunteers were recruited from the local university (UNESP) through pamphlets, online media, personal invitations, telephone calls, and SMS messages. These procedures were recommended by Treweek et al. [15] as strategies to improve participant recruitment.

The inclusion criteria were: male; 18 to 35 years of age; healthy (self-report); not having practiced Pilates prior to the study; not a smoker or an alcoholic; not presenting with a metabolic, cardiac, or endocrine disorder; with no arrhythmia; not using drugs that influence the autonomic modulation of the heart; and without physical limitations such as musculoskeletal, inflammatory, or neurological diseases that would prevent them from doing Pilates.

Individuals who suffered from a musculoskeletal injury during training, those who attended less than 85% of training sessions, those who failed to progress between the three levels of the Pilates method, those who were unable to respond adequately to subjective scales, and those with errors in the captured RR intervals were excluded from the study. Participants were instructed to maintain their daily dietary routine, to abstain from taking anti-inflammatory medications and analgesics, and not to perform any other type of exercise during the intervention period. These requests were reinforced during the training period and monitored by self-report [16].

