### Primary outcome

Quantification of the internal training load was evaluated in each training session with the three monitoring tools: SPE [6], HR [18], and HRV [18]. For the monitoring to be considered successful, two of the three monitoring tools must yield significant results. In addition, the correlation between SPE and HR should be moderate to high so that they can be used in clinical practice as low cost and easily applicable tools.

The SPE consists of a scale proposed by Borg where the participants choose the descriptor and number that best represents their psychophysiological stress in the training session [6]. It is a scale from 6 to 20 points, where 6 means “no effort” and 20 means “maximum effort.” To avoid biased responses, the question was standardized as: “From 6 to 20 points, how do you rate your perception of effort now?” All responses were recorded in individual records. The participants had previously been made familiar with the scale [6].

Prior to the sessions, participants were told how to estimate their SPE. It was explained to them that during the exercises it was necessary to perceive how much effort they were using so that every 5 minutes during a session they could estimate the SPE according to their individual perception for how exhausting the exercises were.

In addition, 15 min after the end of each session, the participants estimated the SPE again [6]. This final SPE was multiplied by the duration of the session in minutes, and the product represents the internal load in arbitrary units. The intensity of the session was classified into three zones according to the Borg scale used by Moreira et al. [19].

Quantification of the internal load training using the HR was performed using the TRIMP method. This evaluates the volume and intensity of the session through specific scores in each training zone, as proposed by Edwards [18, 20].

In addition to these methods for monitoring the training load, HRV was analyzed. The weekly mean of rMSSD (rMSSDmean) expressed in milliseconds and the weekly intra-individual coefficient of variation of rMSSD (rMSSDcv) expressed as a percentage will be used [21, 22]. These indices will be transformed to logarithms to mitigate outliers and simplify the analysis.

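### An undefined exclusion for inadequate scale responses selects the sample partly on how SPE, one of the three primary monitoring tools, performs, and it contradicts the intention-to-treat statement

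*Protocol article*

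**What the plan says.** All references are to the protocol article.

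- **Participants.** One paragraph gives the inclusion criteria. A separate paragraph lists exclusions. It opens with "Individuals who suffered from a musculoskeletal injury during training, those who attended less than 85% of training sessions", goes on to failure to progress between the three levels, then "those who were unable to respond adequately to subjective scales", and ends with "those with errors in the captured RR intervals were excluded from the study". What counts as an adequate response is not stated, and neither is the time at which it is judged.
- **Background.** The hypothesis speaks of "proving that SPE, HR, and HRV are useful tools for monitoring the progression of Pilates training loads".
- **Primary outcome.** "Quantification of the internal training load was evaluated in each training session with the three monitoring tools": SPE, HR and heart rate variability (HRV). Success requires significance for at least two of these. A further condition links the two low-cost tools: "the correlation between SPE and HR should be moderate to high so that they can be used in clinical practice". SPE is rated from 6 to 20, every 5 minutes during a session and again 15 minutes after it.
- **Statistical analysis.** Everyone in the initial assessment is to be analysed by intention to treat, with the poorest result seen in the study group substituted. A correlation of 0.3 to 0.5 is called moderate. Cutoffs for load increments with SPE and the HRV indices come from ROC curves.
- **Trial status.** 58 men were assessed, four were excluded and 54 were randomized. Recruitment is complete.

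**The concern.** Whether people can use the scale is part of what the trial claims for it: the correlation condition is there "so that they can be used in clinical practice as low cost and easily applicable tools". Yet men who cannot answer the scale adequately are to be removed. The SPE load, the SPE–HR correlation and the SPE cutoffs would then be estimated only in men for whom the scale worked. A practitioner who adopts SPE on this evidence meets clients of both kinds. The success rule contains no count of scale failures that would make the selection visible.

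The same sentence does this to a second primary tool, since men with errors in their RR recordings are also excluded.

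The exclusion also cannot stand beside the intention-to-treat statement. An analyst following Participants drops these men; one following Statistical analysis keeps them. Without a criterion for adequacy, two analysts could also drop different men.

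**Working it through.** **1. The plan's own figure.** With a difference of 19.02 ms, SD 23.94 ms, two-sided 5% and 80% power, the normal approximation gives n = 2 × (1.960 + 0.842)² × (23.94/19.02)² ≈ 24.9, so 25 per group, as stated. Adding 10% gives 27.5; the stated 27 is close. If 0 to 5 Pilates men were lost, power for the rMSSD comparison would run from about 83% to 79%. The issue is therefore one of selection, not power.

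**2. When the clause applies.** No time is stated. Three features point to the training period:
- The item is not in the inclusion paragraph.
- Its neighbours (injury, attendance, failure to progress) can occur only once training is under way.
- Ratings during and after sessions exist only for Pilates men, because controls had only the initial and final evaluations.

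Against this, Table 1 lists the SPE scale at the initial assessment, participants were made familiar with it beforehand, and the reasons for the four exclusions before randomization are not given in the text. Screening cannot be ruled out.

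**3. Exclusion against intention to treat.** Participants removes these men from the study; Statistical analysis keeps all who had the initial assessment. Even if the second governs, substitution does not solve the problem. The article does not say what a worst value is for a load rating or for an SPE–HR pair, and a value taken from men who could use the scale does not register that another man could not.

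**4. Usability shares.** The number of men concerned is not given. Assume k = 1 to 5 of the 27 Pilates men could not use the scale. Among those kept, the share able to use it is 100% by construction. Among all 27 it is (27 − k)/27: 96.3%, 92.6%, 88.9%, 85.2% or 81.5%.

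**5. Effect on the SPE–HR correlation, under one model.** Suppose a share q of men gave full ratings unrelated to HR, with the same means and spread as the others. Then r(all) = (1 − q) × r(retained). The value 0.33 is chosen only for illustration.

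| Men excluded | r(all) if r(retained) = 0.33 | Retained r for which the verdict at 0.3 changes |
|---|---|---|
| 1 of 27 | 0.33 × 26/27 = 0.318 | 0.30 to 0.312 (0.3 × 27/26) |
| 2 of 27 | 0.33 × 25/27 = 0.306 | 0.30 to 0.324 (0.3 × 27/25) |
| 3 of 27 | 0.33 × 24/27 = 0.293 | 0.30 to 0.338 (0.3 × 27/24) |
| 4 of 27 | 0.33 × 23/27 = 0.281 | 0.30 to 0.352 (0.3 × 27/23) |

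The window is narrow. If the unit is 27 men, the 95% Fisher interval for r = 0.33 is tanh(0.343 ± 1.96/√24), about −0.06 to 0.63. A shift of about 0.04 is small beside that.

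**6. Limits of the model.** A man who gives no rating contributes no SPE–HR pair, so r is the same whether or not he is excluded. If excluded men differ in mean or spread, the simple formula no longer holds and the direction of the shift is open.

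**The case against.** A reader might infer three stronger things, and the documents support none of them.

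- **That failures of SPE can never count against it.** The intention-to-treat statement, taken at its word, brings excluded men back with an unfavourable value. This stands: the defect is a contradiction between two sections, plus a rule that does not record failure. It is not a settled removal.
- **That men were removed because their SPE did not follow their HR.** The wording more naturally describes not understanding or not completing a scale. The question was standardized, participants were familiarized, and independent evaluators collected the training data. The clause refers to scales in the plural and may also cover the pain scale. The missing criterion leaves room for such a judgement, but nothing says that it was made.
- **That the exclusion pushes the correlation over the threshold.** This needs assumed numbers, full but unrelated ratings from the excluded men, and a retained r just above 0.3. Trial status mentions no exclusion after randomization and reports that all participants are still attending.

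Two further points are fair. SPE is one of three tools and the correlation is one added condition, so scale usability is not the whole primary question. And if the clause was applied before training, it limits generalizability more than it biases the analysis.

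What remains is that the clause, as written, conditions the sample on a tool under test, has no criterion, and conflicts with the analysis set.

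**Conclusion.** The point holds as a flaw in the rule. The exclusion selects the sample partly on the performance of one of the three primary tools, the RR clause does the same for HRV, and both contradict the stated intention-to-treat set. This follows from the text alone, although applying it to session ratings rests on reading the clause with its neighbours in the list, because its timing is not stated.

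The size and direction of any effect on the SPE–HR correlation cannot be established from the document. With three exclusions, and only under the equal-spread, zero-correlation model, a verdict at 0.3 would change for a retained r of about 0.30 to 0.34. The share of men able to use the scale would be 100% among those kept, against 96.3% to 81.5% of all 27 if one to five men were affected. Those counts are assumptions, and the article does not plan to report such a share.

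The correction is worth making because it settles the contradiction at almost no cost.

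**What to change.** - Reconcile Participants with Statistical analysis by removing the scale-response clause from the analysis exclusions.
- Keep all men randomized to Pilates, and all their valid SPE ratings, in the SPE load, SPE–HR correlation and ROC analyses. Set to missing only a rating that was not given or lies outside 6 to 20.
- Beside the primary result, report the number and share of men and sessions without a usable SPE rating, and likewise without a usable RR recording. Word the usability conclusion so that it takes these into account.

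A comprehension screen before randomization can no longer be added, because recruitment is complete. The changes above remain open: the analyses are described as still to come, and the responses are kept in individual records. The cost is a change of wording and one extra descriptive count. The downside is a possibly less favourable SPE result.

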### Randomization

Prior to randomization, baseline data were collected from participants who meet the eligibility criteria and had signed the informed consent form. To maintain the blinding, randomization by group (Pilates group or control group) was performed by another researcher not involved in the recruitment using a computer-generated randomization schedule.

### Details of procedures

#### Study outline

The evaluations were carried out at FCT/UNESP, in a room with controlled temperature and humidity, at the same time of day. For the initial evaluation, after completing the personal information, the participants completed a psychometric questionnaire [17]. Once the anthropometric metrics had been collected for each participant, their body mass index was calculated.

In addition, systolic and diastolic blood pressure, HR, respiratory rate, and oxygen saturation were measured. Then, the participants were sent to a quiet room where a cardiofrequency meter (V800, Polar Electro Oy, Kempele, Finland) recorded their HR beat to beat for 20 min for later analysis of HRV.

The Pilates training began after a week with three familiarization sessions. At the start of each training session, cardiorespiratory measures (systolic blood pressure, diastolic blood pressure, respiratory rate, HR, and oxygen saturation) and pain (visual analogue scale) were measured, and a psychometric questionnaire was completed, as the basal control. To measure the progression of load, HR, SPE, and vagal indices of HRV were used. These metrics were collected during the exercises. HR was measured and recorded on the SPE scale every 5 minutes, and the RR intervals were recorded during the whole session. At the end of each session, the cardiorespiratory metrics and pain (visual analogue scale) were measured, and the psychometric questionnaire was completed. After 15 minutes of rest, the volunteers underwent the final HR measurements and completed the SPE scale again. The sessions are shown in Fig. 2.

**Fig. 2 Fig2:**
[figure not shown]
Study outline. VAS visual analog scale BP blood pressure, HR heart rate, *f* respiratory rate, SatO_2_ oxygen saturation, SPE subjective perception of effort

At the end of the 36 Pilates training sessions, the final evaluation was carried out. This included cardiorespiratory measures, the psychometric questionnaire, and HRV. The control group underwent only the initial and final evaluations, like the Pilates group.

### Pilates exercises

The exercises are shown in Additional file 1. The exercise sequences were divided in different ways to make the training more varied and to avoid dropouts (Additional file 2). The exercise schedule was produced by us based on an extensive bibliographical survey of Pilates exercises and their progression. We considered the degree of difficulty of each exercise as well as the dependence between volume and intensity.

### Primary outcome

Quantification of the internal training load was evaluated in each training session with the three monitoring tools: SPE [6], HR [18], and HRV [18]. For the monitoring to be considered successful, two of the three monitoring tools must yield significant results. In addition, the correlation between SPE and HR should be moderate to high so that they can be used in clinical practice as low cost and easily applicable tools.

The SPE consists of a scale proposed by Borg where the participants choose the descriptor and number that best represents their psychophysiological stress in the training session [6]. It is a scale from 6 to 20 points, where 6 means “no effort” and 20 means “maximum effort.” To avoid biased responses, the question was standardized as: “From 6 to 20 points, how do you rate your perception of effort now?” All responses were recorded in individual records. The participants had previously been made familiar with the scale [6].

Prior to the sessions, participants were told how to estimate their SPE. It was explained to them that during the exercises it was necessary to perceive how much effort they were using so that every 5 minutes during a session they could estimate the SPE according to their individual perception for how exhausting the exercises were.

In addition, 15 min after the end of each session, the participants estimated the SPE again [6]. This final SPE was multiplied by the duration of the session in minutes, and the product represents the internal load in arbitrary units. The intensity of the session was classified into three zones according to the Borg scale used by Moreira et al. [19].

Quantification of the internal load training using the HR was performed using the TRIMP method. This evaluates the volume and intensity of the session through specific scores in each training zone, as proposed by Edwards [18, 20].

In addition to these methods for monitoring the training load, HRV was analyzed. The weekly mean of rMSSD (rMSSDmean) expressed in milliseconds and the weekly intra-individual coefficient of variation of rMSSD (rMSSDcv) expressed as a percentage will be used [21, 22]. These indices will be transformed to logarithms to mitigate outliers and simplify the analysis.

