### Statistical analysis

Descriptive statistics will be used, and the results presented as means, errors, standard deviations, percentages, and absolute numbers. The normality of the data will be evaluated through a Shapiro–Wilk test. In the comparison of the population profile and the cardiorespiratory, autonomic, and psychometric measures in the initial and final evaluations, the paired *t* test will be used for normal data or the Wilcoxon test for non-normal data. In the comparison between the groups, the unpaired *t* test or Mann–Whitney test will be used depending on the normality of the data, with the significance level set at *p* < 0.05. Differences based on magnitudes (Δ = final value – initial value) will also be calculated [35, 36] to verify the differences between the initial and final time points.

To analyze weekly differences in training loads using the SPE, HR, and HRV indices (ln rMSSDweekly and ln rMSSDcv) over the 12-week study duration, magnitude-based inferences will be calculated [36].

For ln rMSSDweekly, the smallest worthwhile change was set at 3% [37]. For SPE, HR, and ln rMSSDcv, the smallest worthwhile change is defined as 0.2 × between-subject standard deviation. The quantitative chances to find differences in the variables to be tested will be assessed qualitatively as follows: <1% almost certainly not, 1–5% very unlikely, 5–25% unlikely, 25–75% possible, 75–95% likely, 95–99% very likely, and >99% certain. If the chances of having higher and lower results are both >5%, the true difference was assessed as nuclear [35]. The magnitude of the effect size will be qualitatively interpreted using the following thresholds: <0.2 trivial, 0.2–0.6 small, 0.6–1.2 moderate, 1.2–2.0 large, 2.0–4.0 very large, and >4.0 nearly perfect [35].

To determine the correlations (dose–response) between ln rMSSD, HR, and SPE, Pearson’s or Spearman’s correlation will be used according to the normality of the data. The threshold used to evaluate the correlations quantitatively will be based on Hopkins [35] using the following criteria: <0.1 trivial, 0.1–0.3 small, 0.3–0.5 moderate, 0.5–0.7 large, 0.7–0.9 very large, and >0.9 almost perfect.

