## Discussion

Previous systematic reviews have found a beneficial effect of Pilates on risk factors for various diseases, as well as positive responses in outcomes such as strength, flexibility, low back pain, and quality of life, among others [2, 39, 40]. However, the low methodological quality of previous studies and the lack of load monitoring of the exercises do not allow definitive conclusions to be drawn about the effect of the Pilates method. Moreover, there have been few studies investigating the effects of Pilates on the cardiac autonomic nervous system.

Methodological characteristics commonly found in studies published in the literature include lack of concealed allocation, no intention-to-treat analysis, unblinded assessors, lack of standardization of training on biological principles, and low familiarization of participants with the method. This study is a parallel randomized clinical trial to measure the effectiveness of the Pilates method on the cardiac autonomic nervous system and, mainly, to analyze methods of monitoring training loads.

The best measures for quantifying the internal load are SPE and HR, because they are cheap and simple to use. They can be measured by any healthcare professional. HRV is also important as an early and sensitive indicator of health impairment; however, correct analytical use of this tool requires detailed knowledge.

The training protocol described in this study was based on the most recent literature. A strength of the study is the parallel randomized clinical trial design with an intention-to-treat analysis. Moreover, the protocol is easy to replicate. However, a limitation is the inability to blind participants to their allocation.

This study may contribute by providing further information on the real autonomic benefits provided by this type of physical exercise and can be used to guide practitioners in prescribing the method, as well as offering more support to practitioners.

Note that this study uses the checklist of items for protocol studies to minimize bias. It was prospectively registered. The outcomes will be disseminated through publications in scientific journals and presentations at area congresses.

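### The two-of-three success rule and the SPE–HR correlation can both be met, and the low-cost claim made, although SPE or HR on its own failed to track load

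*Protocol article*

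**What the plan says.** The Background (last paragraph) states the hypothesis about tools by name. It speaks of "proving that SPE, HR, and HRV are useful tools for monitoring the progression of Pilates training loads", and expects a good SPE–HR correlation, "thus giving practitioners two simple low-cost monitoring tools". The Discussion repeats the emphasis on that pair: "The best measures for quantifying the internal load are SPE and HR, because they are cheap and simple to use".

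The Primary outcome section sets the decision rule: "For the monitoring to be considered successful, two of the three monitoring tools must yield significant results". Which two is not fixed. The next sentence adds a condition: "In addition, the correlation between SPE and HR should be moderate to high so that they can be used in clinical practice". The Statistical analysis section gives the scale for that correlation, with "0.3–0.5 moderate". For the weekly loads of all three tools the same section says that "magnitude-based inferences will be calculated", and it sets a smallest worthwhile change for SPE, for HR and for each of the two HRV indices.

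**The concern.** The hypothesis and the intended message are about individual tools, above all SPE and HR. The decision rule is a count across the three tools. A count of two can be reached as SPE plus HRV or as HR plus HRV, and in either case one of the two low-cost tools has not shown the load progression. The extra condition asks whether SPE and HR agree with each other, not whether each of them followed the load over the 12 weeks.

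What is at stake is the conclusion that practitioners would act on. A trial that meets its own success rule could recommend SPE and HR as a pair although the result for one of them was negative.

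**Working it through.** **1. Is there a figure in the plan to reproduce?** Not for this rule. The only power figure is in Sample size calculation: difference 19.02 ms, SD 23.94 ms, two-sided 5%, power 80%, giving 25 per group. It reproduces with the normal approximation: 2 × (1.960 + 0.842)² × (23.94/19.02)² ≈ 24.9, so 25. It concerns rMSSD with a size per group. The weekly load analysis concerns the training sessions, which the control group does not have, so this 80% cannot be carried over to the three tools.

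**2. One outcome set against each stated condition.** Suppose SPE and HRV are positive, HR is negative, and the SPE–HR correlation is 0.35.

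| Condition or claim in the article | Result |
|---|---|
| Two of three tools significant (Primary outcome) | met, by SPE and HRV |
| SPE–HR correlation at least moderate (Primary outcome; scale in Statistical analysis) | met, 0.35 exceeds 0.3 |
| SPE, HR and HRV all useful (Background) | not supported for HR |
| SPE and HR as the two low-cost tools (Background) | correlation met, but HR did not track load |

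The same holds with SPE and HR exchanged. At the lower limit for a moderate correlation the shared variance is 0.3² = 0.09, or 9%. SPE and HR are both taken every 5 minutes within sessions, so they can move together within a session, or differ together between men, without either one changing over the weeks.

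**3. How often a two-of-three pass contains a failed tool (illustration).** Let p be the chance that a tool is positive. The article gives no such value, so p is an assumption. For independent tools:

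- P(at least two) = 3p²(1 − p) + p³
- P(all three) = p³
- Share of passes with a failed tool = 3p²(1 − p) / P(at least two)

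At p = 0.8: 3 × 0.64 × 0.2 + 0.512 = 0.384 + 0.512 = 0.896. The share with a failed tool is 0.384/0.896 = 43%. In two of the three equally likely patterns the failed tool is SPE or HR: 0.256/0.896 = 29%.

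At p = 0.6: 0.432/0.648 = 67%. At p = 0.9: 0.243/0.972 = 25%.

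**4. Correlated tools.** Independence is unlikely, since HR and rMSSD come from the same sessions and SPE is expected to follow HR. Simulation of correlated test statistics (1,000,000 draws, 80% power each, two-sided 5%) gives:

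| Correlation of test statistics | At least two | All three | Share of passes with a failed tool | Share with SPE or HR failed |
|---|---|---|---|---|
| 0.3 | 85.8% | 56.8% | 34% | 23% |
| 0.5 | 83.9% | 61.2% | 27% | 18% |
| 0.7 | 82.1% | 65.9% | 20% | 13% |

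**5. One low-cost tool without any signal.** Let HR be positive 5% of the time and the other two 80%, independently. P(at least two) = 0.64 × 0.95 + 0.64 × 0.05 + 0.05 × 0.32 = 0.608 + 0.032 + 0.016 = 0.656. In 60.8% of trials the count is met with HR negative. With correlations of 0.3 to 0.7 the pass rate is 68% to 72%.

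None of the figures in steps 3 to 5 applies the SPE–HR correlation condition. The pass rates are therefore upper limits for the two conditions together.

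**6. False positives.** If no tool carries signal and each has a 5% error rate, the count is met in 0.7% of trials under independence and about 3.2% at correlation 0.7. Error inflation is not the issue.

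**The case against.** The strongest reply is that the rule's subject is the monitoring as a whole. No sentence says that a failed tool will be reported as having worked. The Background sentence is a hypothesis, and setting a success threshold below the full hypothesis is a legitimate design choice. A reader might infer that the article commits the trial to endorsing a tool that failed, or that it flatly contradicts itself. The documents do not support either inference: such an endorsement follows only if the rule is joined to the Background claims and the correlation clause.

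That clause can also be read as a further necessary condition, on top of the tools' own results, rather than as enough by itself. The wording allows both readings. In addition, the Statistical analysis section already examines each tool against its own threshold, so a negative result for one tool would be visible.

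The percentages are open to objection too. The assumed chances are not in the document. The word *significant* has no stated test behind it here, because the weekly loads are assigned to magnitude-based inference. And if HR did not follow load while SPE did, the correlation condition would be harder to meet, although correlation between men could still satisfy it.

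All of this stands, and it limits the point to what the text permits. It does not close the gap: no sentence requires SPE and HR each to be positive before the pair is put forward, and none confines the conclusion to the tools that passed. The per-tool results show a failure but do not enter the rule.

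**Conclusion.** The point holds as a mismatch between the success rule and the claims attached to it. As written, the rule can be met and the low-cost claim made while SPE or HR individually failed. The text permits that outcome and does not compel it. This conclusion rests on the wording alone and needs no numerical assumption.

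The size is illustrative only. It depends on the assumed 80% per tool, on the degree of correlation, and on leaving out the SPE–HR condition. The figures of 43% under independence and 34% to 20% under correlation show that such a pass would not be a rare accident under those assumptions. They do not forecast this trial, and the 65.6% in step 5 is not the frequency with which HR would be cleared for practice.

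**What to change.** 1. State the conclusion separately for SPE, HR and HRV, from the per-tool weekly analyses already planned under Statistical analysis, and say what counts as a positive result for each.
2. Make the low-cost claim only if SPE and HR are each individually positive and the correlation criterion is also met.
3. If two-of-three stays as the headline, word it as at least two tools having tracked load, name any tool that failed, and bring the hypothesis in the Background into line.

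No new data are needed. Trial status reports that recruitment is complete and that data were collected in June 2019, so this changes a primary success rule late. It should be recorded as a dated, justified change before the results are read.

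The price is a pair claim that is harder to reach. In the 80% illustration with independent tools, SPE and HR are both positive with probability 0.8² = 64%, against 89.6% for the count. At correlation 0.7 the simulated figures are 82.1% − 10.8% = 71.3% against 82.1% (10.8% being passes in which SPE or HR failed). All are before the correlation condition.
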